### Statistical power

We hypothesized that differences in HIV-free infant survival and MTCT between Option B+ (2017 estimates) and the pre-Option A standard of care (2012 estimates) will be greater than the differences between Option B+ (2017–18 estimates) and Option A (2014 estimates). Therefore, sample size calculations for the community surveys were conducted targeting the comparison between 2014 and 2017–18 estimates, as described below.

Sample size calculations were based on the formula for unadjusted comparison of proportions within matched pairs (where a “pair” is two measurements of the outcome within the same catchment area e.g. MTCT in a given facility in 2014 and in 2017–18) [21]. Findings from the 2012 survey estimate an average ANC prevalence of 12.5% among mothers in our catchment areas, with 9% of HIV exposed 9–18 month old infants being infected and 10% of HIV-exposed infants being deceased or infected with HIV [9]. In 2014 ANC prevalence was 13.6% among mothers in our catchment areas and the proportion of HIV-exposed infants who were deceased or HIV-infected had dropped to 4.8% [22]. In Zimbabwe the national targets for Option B+ are 95% HIV-free infant survival and less than 5% MTCT. Consequently, we calculated the sample size needed to detect a reduction from 2014 outcome proportions to 3.4% HIV infection or death in 2017–18.

Based on our 2012 and 2014 survey experience, we presume the 2017–18 survey will have a survey refusal rate of 2% and a value of 0.25 for the coefficient of variation (k_m_). Using a two sided-test at a 5% level of significance and a desired power of 80%, we would require a harmonic mean greater than 4 HIV-exposed infants (i.e., infants whose mothers are HIV-infected) per catchment area. We expect that the prevailing trend of decreasing ANC prevalence will continue [23] and therefore assume that ANC prevalence will have decreased to 11.5% by 2017–18. Taking into account variability in both catchment area size and underlying HIV prevalence among pregnant women across PSUs (again, based on our 2012 and 2014 data) we estimate that we will need a sample 13,000 pairs in 2017–18. Using the above assumptions we would have 80% power to detect a difference in HIV-free infant survival between Option A and Option B+.

For mothers at 19–36 months post partum, under the assumption of a 11.5% HIV prevalence among mothers in 2017–18, and taking into account variation in prevalence and refusal rates similar to those observed in the 2012 and 2014 surveys, we estimated that, in order to measure the proportion of mothers who continued ART after weaning, we would require a sample of approximately 1800 mother-infant pairs, of which approximately 200 mothers are expected to be HIV-infected.

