### Sampling strategy

In the first stage of our multi-stage sampling process, we selected catchment areas of health facilities offering PMTCT services within each district of five provinces of Zimbabwe as primary sampling units (PSUs), 157 of 699 catchment areas were randomly selected with probability proportionate to the number of facilities in each district. In 2012 and 2014, the second stage of sampling selected eligible mother-infant pairs living in the catchment areas of these 157 facilities. Women are considered eligible if they are at least 16 years old, able to respond to questions in English or Shona/Ndebele and are living in a catchment area household.

Eligible mother-infant pairs were selected using a pre-determined sampling fraction that was a function of the number of mother-infant pairs identified. In catchment areas with fewer eligible pairs, a greater proportion were sampled to ensure a minimum sample of 50 mother-infant pairs from each catchment area. During the first two survey rounds, eligible mother-infant pairs were identified based on information pooled from: 1) village health workers (VHWs) and 2) immunization registers from selected facilities and neighboring facilities (to identify women residing in sampled facilities who accessed services at adjacent facilities) [9]. Further, mothers identified using (1) and (2) were asked to identify other eligible infants in their neighborhood [9].

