Sampling fractions for EAs within each catchment area were chosen to target selection of roughly 50 mother-infant pairs per catchment area. Sampling fractions used in in the 2014 survey round to select eligible mother-infant pairs in each catchment area were used as a base to select a comparable proportion of EAs from each catchment area for the 2017–18 round. Adjustments were made to sampling fractions to mandate a minimum selection of 7 EAs per clinic catchment area, or all EAs if there were fewer than 7 EAs associated with a clinic catchment area. In each selected EA, village health workers (VHW) are trained by and work in conjunction with survey staff to conduct a full census of all households in the selected EAs. The VHWs and survey teams use area maps to visit all identified structures, and record the number of potentially eligible mothers and infants by visiting households and conducting a short screening survey to ascertain the presence of eligible mother/caregiver-infant pairs. Within the selected EAs, all eligible mothers who have given birth 9–18 months prior, and all infants 9–18 months old are selected for inclusion in the survey. We will also sample 10% of mothers 19–36 months postpartum in order to assess longer term engagement in care following the end of the breastfeeding period.

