
### Analyses

All statistical analyses will be conducted using the software package STATA version 15 (StataCorp, Texas). The data will be weighted to account for the multi-stage stratified cluster design and survey non-response. For the first two rounds of the survey weighting was done to account for the selection of catchment areas within districts, mother infant pairs within catchment areas and for survey non-response. For the final round survey, weighting is the same for the selection of clinics within districts, but differs for the later stage weighting. For this survey, weights will be constructed for the probability of being in a selected EA within the catchment area, the probability of complete census data within EAs (census non-response), and survey non-response among identified eligible mother infant pairs. GPS coordinates collected for each structure in selected EAs and will be used to assess whether census non-response is associated with distance from the clinic or distance from the center of the EA.

To assess the population-level impact of Option B+ (Objective 1), we will estimate and compare the population-level differences in MTCT and HIV-free infant survival among infants born after Option B+ is implemented (2017–18 estimates) and those born under the standard of care prior to Option A estimates (2012 estimates). Next, we will estimate the differences in these outcomes between infants born after Option B+ is implemented (2017–18 estimates) and those born under Option A guidelines (2014 estimates). These estimates will be generated by treating the two conditions compared in each analysis as matched pair observations for each catchment area, adjusting only for the sampling design through weighting. As with all pre-post evaluation designs, there is a concern that temporal trends, unrelated to the intervention, may be responsible for observed differences in the outcomes. To address this concern, we will also estimate differences in MTCT and HIV-free survival proportions adjusted for facility- and individual-level covariates not affected by the intervention. For example, in addition to demographic and socioeconomic characteristics such as the age of the mothers and infants, we will adjust for women’s ART use before pregnancy. To adjust for these factors, we will apply targeted maximum likelihood estimation, as well as standard parametric regression and inverse probability weighted methods.

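### The stated 80% power for Option A versus Option B+ has no allowance for the survey weights used in the primary analysis, and it does not follow from the printed inputs even without weights

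*Protocol article*

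**What the plan says.** The Statistical power section of the protocol article sizes the community survey on the 2014 versus 2017–18 comparison: "Sample size calculations were based on the formula for unadjusted comparison of proportions within matched pairs", a pair being the same catchment area measured in the two rounds. The effect to detect is "a reduction from 2014 outcome proportions to 3.4% HIV infection or death in 2017–18", from 4.8% in 2014. The other inputs are "a value of 0.25 for the coefficient of variation", a two-sided 5% test, 80% power, 2% refusal, a harmonic mean above 4 HIV-exposed infants per area, 11.5% maternal prevalence and 13,000 pairs. The step to 13,000 is said to allow for variation in catchment size and in prevalence.

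The Analyses section defines the primary estimate as "treating the two conditions compared in each analysis as matched pair observations for each catchment area, adjusting only for the sampling design through weighting". The weights cover selection of areas within districts, selection within areas, and non-response.

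On the take per area, the Sampling strategy section says of 2012 and 2014: "In catchment areas with fewer eligible pairs, a greater proportion were sampled to ensure a minimum sample of 50 mother-infant pairs from each catchment area". Of 2017–18 it says: "Sampling fractions for EAs within each catchment area were chosen to target selection of roughly 50 mother-infant pairs per catchment area". The 2014 fractions serve as the base, and at least 7 enumeration areas are taken per catchment area, or all of them where there are fewer.

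**The concern.** The sizing formula gives each catchment area the same weight; the primary estimate does not. Areas were drawn in proportion to the number of facilities per district, so each has roughly the same chance of selection. Small areas are then sampled more heavily than large ones, so the weights differ with catchment size. A harmonic mean of exposed infants deals with unequal counts in an equally weighted comparison, not with unequal weights.

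What is at stake is the reading of Objective 1b, the comparison for which the survey was sized. A non-significant weighted difference between Option A and Option B+ would be judged against a stated 80% and could be taken as evidence of no added benefit, when the design had far less chance of showing one.

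**Working it through.** **Inputs.** From Statistical power: p0 = 0.048, p1 = 0.034, k_m = 0.25, two-sided 5%, 80% power, prevalence 11.5%, refusal 2%, 13,000 pairs. From Sampling strategy: c = 157 areas. The article cites its formula without printing it. The check uses the standard form for pair-matched clusters:

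c = 2 + (1.96 + 0.84)² × V / (p0 − p1)², with V = [p0(1 − p0) + p1(1 − p1)]/m + k_m²(p0² + p1²)

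and power = Φ(√[(c − 2)/V] × (p0 − p1) − 1.96), where m is the harmonic mean number of exposed infants per area, taken as equal in the two rounds.

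**Step 1: try to reproduce the 80%.**
- Binomial part: 0.045696 + 0.032844 = 0.07854. Between-area part: 0.0625 × 0.00346 = 0.000216.
- At m = 4: V = 0.019635 + 0.000216 = 0.01985; √(155/0.01985) × 0.014 = 1.237; power = Φ(1.237 − 1.96) = 23%. The formula would ask for about 797 areas.
- At the planned sample: 13,000/157 = 82.8 pairs per area; 82.8 × 0.115 × 0.98 = 9.3 exposed. V = 0.00863; power = Φ(1.876 − 1.96) = 47%. This uses the arithmetic mean, which the harmonic mean cannot exceed.
- At the target of 50 per area: 50 × 0.115 × 0.98 = 5.6 exposed; power = 31%.
- For 80%: m = 0.07854/(155 × 0.000196/7.849 − 0.000216) = 21.5 exposed per area, or 21.5/(0.115 × 0.98) × 157, about 30,000 pairs.

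The 80% is not reproduced.

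**Step 2: does another reading rescue it?**
- Setting k_m = 0 gives 24% at m = 4 and 48% at m = 9.3, so no value of k_m does so.
- Ignoring clustering, 13,000 × 0.115 × 0.98 = 1,465 exposed infants per round give 48%; 3,148 per round would be needed.
- A one-sided test gives 34% at m = 4 and 59% at m = 9.3.
- A different 2014 count matters little. At 13.6% prevalence and an assumed 50 to 83 pairs per area in 2014, power with 9.3 exposed in 2017–18 is 40% to 51%.
- Treating the 2014 result as free of sampling error gives 81% at m = 9.3 (48% at m = 4). That is not a comparison of two measured proportions within pairs.

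**Step 3: effect of weighting at 13,000 pairs.** For a weighted mean of area differences with equal take, the variance is inflated by about 1 + CV², with CV the coefficient of variation of the area weights. The article gives no CV, so 0.25 to 1.0 is assumed. Area sizes were simulated as lognormal over 157 areas, with weights proportional to size and starting from about 47%:

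| CV of area size | Equal take: variance ratio, power | 50 per area plus a part proportional to size: variance ratio, power | Take proportional to size: variance ratio |
|---|---|---|---|
| 0.25 | 1.06, 45% | 1.01, 46% | 0.95 |
| 0.5 | 1.25, 39% | 1.05, 44% | 0.81 |
| 0.75 | 1.55, 33% | 1.09, 42% | 0.66 |
| 1.0 | 1.97, 27% | 1.13, 40% | 0.52 |

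The variance ratio compares the weighted with the equally weighted estimate under the same take. For equal take, the closed form with 1 + CV² gives 44%, 39%, 32% and 26%.

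**Step 4: which take applies?** A take of 50 in each area totals 157 × 50 = 7,850 pairs, not 13,000, and 13,000 pairs mean about 83 per area. The article therefore supports neither a fixed nor a proportional take.

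**The case against.** The best defence has three parts.

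First, an article condenses the full protocol, and an unprinted design effect is not in itself an error. That stands: silence on weights alone would not justify this point. But the article prints a power figure together with its inputs, and the figure does not follow from them.

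Second, the sample size text says that catchment size and prevalence were taken into account using earlier data. That explains why 13,000 exceeds what a bare harmonic mean of 4 would need. It does not restore 80%, because even the most favourable reading of 13,000 pairs, with equal counts in every area, gives about 47%.

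Third, a reader might infer that 80% is the correct unweighted power and that weighting takes a definite share off it. The documents support neither half. The unweighted formula reaches 80% only at about 21.5 exposed infants per area, a design the article never describes. The direction of the weighting effect rests on a near-equal take: 50 was a minimum in 2012 and 2014, it is an approximate target in 2017–18, and the mean implied by 13,000 pairs is about 83. If counts rise with catchment size, weighting can be nearly free or can reduce the variance relative to equal weighting.

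Nor does the primary analysis abandon the matched-pair structure. The pairing is the same in both sections; only the weighting differs.

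**Conclusion.** The point holds in a limited form. The 80% was derived from a formula without a term for the weights that the primary analysis applies, and the printed inputs do not yield it: they give about 23% at 4 exposed infants per area and about 47% at 13,000 pairs. This shortfall is the larger part of the problem. The added effect of weighting is conditional: a fall from about 47% to between 45% and 27% if the take is near-equal, little or no loss if it rises with size. Its size cannot be fixed from the article.

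Before weighting, the fall from 4.8% that is detectable with 80% power is to about 2.8% at 9.3 exposed infants per area, or to about 1.9% at 4, rather than to 3.4%. These figures assume equal exposed counts in 2014 and 2017–18 and the formula shown.

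The finding concerns Objective 1b. It should not be read as saying that the whole evaluation lacks power: for 10% in 2012 against 3.4%, the same unweighted formula gives over 99% even at 4 exposed infants per area.

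**What to change.** In Statistical power, recompute power or the minimum detectable difference for the weighted paired difference defined in Analyses. Use the actual 2012 and 2014 area weights, taking the effective number of areas as (sum of weights)² / (sum of squared weights) where the take is near-equal, or the full weighted variance where it is not. Use the expected exposed infants per area in each round, add the effect of unequal weights within areas, and replace the 80% with the result. State the formula and the harmonic mean actually used, since 4 does not give 80%.

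In the same revision, reconcile the target of about 50 pairs per area (7,850 in total) with the 13,000 pairs, and say how the take is expected to vary with catchment size. That settles the direction of the weighting effect.

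The cost is a short calculation on weights that the sponsor should already hold from the earlier rounds. No added enrolment is needed. The drawback is a less favourable stated power for Option A versus Option B+.

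### The stated requirement of more than 4 HIV-exposed infants per catchment area, and the 80% power for Option B+ versus Option A, do not follow from the plan's own inputs

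*Protocol article*

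**What the plan says.** The Statistical power section chooses the 2014 versus 2017–18 contrast as the one to size on, because the contrast with 2012 is expected to be larger. The method is the "formula for unadjusted comparison of proportions within matched pairs", where a pair is the same catchment area measured in two rounds. The baseline is that "the proportion of HIV-exposed infants who were deceased or HIV-infected had dropped to 4.8" per cent by 2014. The alternative is given as: "we calculated the sample size needed to detect a reduction from 2014 outcome proportions to 3.4% HIV infection or death".

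The other inputs are a coefficient of variation of 0.25, a 2% refusal rate, a two-sided 5% test, 80% power and 11.5% prevalence in 2017–18. The number of catchment areas, 157, is in the Sampling strategy section.

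From these inputs the section concludes that "we would require a harmonic mean greater than 4 HIV-exposed infants (i.e., infants whose mothers are HIV-infected) per catchment area", that this means 13,000 pairs, and finally: "Using the above assumptions we would have 80% power to detect a difference in HIV-free infant survival between Option A and Option B"+.

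**The concern.** The effect is a 1.4-point difference between two small proportions. Four exposed infants in each of 157 areas is 628 infants per round, so at 4.8% and 3.4% the two rounds would be expected to have about 30 and 21 events. That is too few to separate the rounds with 80% power, before any clustering is counted.

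This contrast is Objective 1b, and the section presents it as the one that drives the survey's size. A reader who accepts the 80% would treat an inconclusive comparison as stronger evidence against an added benefit of Option B+ than the data could supply.

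**Working it through.** **Inputs.** p0 = 0.048, p1 = 0.034, k = 0.25, two-sided 5%, 80% power, prevalence 11.5%, refusal 2%, 13,000 pairs (Statistical power); c = 157 areas (Sampling strategy). The article does not print its formula. I used the standard matched-pair cluster form:

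c = 2 + (1.960 + 0.842)² × [p0(1−p0)/n + p1(1−p1)/n + k²(p0² + p1²)] / (p0 − p1)²

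**Trying to reproduce the stated figure.** Solve for n, the harmonic mean of exposed infants per area per round:

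- p0(1−p0) + p1(1−p1) = 0.045696 + 0.032844 = 0.07854
- k²(p0² + p1²) = 0.0625 × (0.002304 + 0.001156) = 0.000216
- (c − 2)(p0 − p1)² / 7.849 = 155 × 0.000196 / 7.849 = 0.003871
- n = 0.07854 / (0.003871 − 0.000216) = 21.5

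The stated figure is more than 4. Since the source formula is not shown, I varied what could differ:

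| Variant | n per area |
|---|---|
| Additive constant 0, 1 or 2 | 21.2 to 21.5 |
| k = 0 (no residual between-area variation) | 20.3 |
| One-sided 5% | 16.7 |
| Both proportions moved within rounding | 18.6 to 25.2 |
| Plain two-proportion test, 3,148 per round / 157 | 20.1 |
| 2014 proportion treated as known exactly | 8.6 |

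None gives a value near 4. Binomial sampling variation dominates, so the choice of k hardly matters.

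**Power at the stated floor.** With n = 4 in both rounds the variance term is 0.07854/4 + 0.000216 = 0.01985. SE = √(0.01985/155) = 0.01132, z = 0.014/0.01132 = 1.24, and power is 23.5%. At n = 4 the formula would need 797 areas.

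**What 13,000 pairs give.** 13,000 × 0.115 × 0.98 = 1,465 exposed infants; 1,465/157 = 9.33 per area. This is an arithmetic mean, so the harmonic mean is no larger.

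**Power with 9.33 per area in 2017–18.** The article does not give the 2014 exposed count, so each row rests on an assumption about it:

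| Assumed exposed infants per area, 2014 | SE | z | Power |
|---|---|---|---|
| 9.33 (equal to 2017–18) | 0.00746 | 1.88 | 47% |
| 11.04 (13,000 pairs × 13.6% × 98% / 157) | 0.00713 | 1.96 | 50% |
| 15 | 0.00662 | 2.12 | 56% |
| 18.66 (twice 2017–18) | 0.00632 | 2.22 | 60% |
| Unlimited | 0.00491 | 2.85 | 81% |

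Reaching 80% would need roughly 220 exposed infants per area in 2014 if 2017–18 has 9.52 per area (refusal ignored: 13,000 × 0.115 / 157), and about 340 if it has 9.33. All rows treat areas as equal in size; in this formula unequal sizes lower the harmonic mean and hence the power.

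**Detectable difference.** With 9.33 per area in both rounds, 80% power is reached for 4.8% versus about 2.8%.

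**The case against.** The strongest objection is that the size of the shortfall is not known. The 2014 round is complete, its exposed count is not in the article, and 2014 prevalence was 13.6% rather than 11.5%. A reader might infer that 47% is a ceiling. It is not: it is the value when 2014 had 9.3 exposed infants per area, and a larger 2014 round raises it. For the same reason, it is not established that a non-significant result is more likely than not if the effect is real. That holds in the equal-rounds case, but not at 56% or 60% power.

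A reader might also scale 21.5 per area up to a required survey: 21.5 × 157 / 0.115 / 0.98, or about 29,900 pairs. That presumes 21.5 per area in both rounds. With 2014 fixed at 9.3 per area, about 29,900 pairs in 2017–18 give only about 57% power, and an unlimited 2017–18 sample only about 68%. No such sample size should be quoted. Nor do the documents show where the figure of 4 came from. Other contrasts give similar values (9% versus 5% gives 4.2; 4.8% versus 2.0% gives 4.3), so any single origin is a guess.

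It is also fair to say that the cited formula is not visible and that a condensed article may leave detail to a fuller document. That excuses the unprinted formula and the missing 2014 count. It does not excuse a result that conflicts with inputs printed beside it, and the spread of variants above shows that the conflict does not depend on the exact formula.

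**Conclusion.** The concern holds as an error of arithmetic in the Statistical power section. For 4.8% versus 3.4% with 157 matched areas, the required harmonic mean is about 21.5 exposed infants per area per round, some five times the stated floor, and power at that floor is about 23%. The planned 13,000 pairs do not give 80% power under any plausible 2014 round: about 47% to 60% over the range from an equal round to one twice as large, and less if catchment sizes vary.

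This rests on the standard matched-pair cluster formula, which is inferred from the article's description and its use of a coefficient of variation, and on assumed 2014 counts. The failure of the stated figures is firm; the exact power awaits the 2014 data.

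**What to change.** In the Statistical power section:

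1. Replace the required harmonic mean of more than 4 with the value that follows from the stated inputs, about 21.5 per catchment area per round, and write out the formula used.
2. Recompute power for 4.8% versus 3.4% from the actual 2014 exposed counts by catchment area and the planned 2017–18 sample, using harmonic means.
3. Replace the 80% claim with that power, and add the difference detectable at 80% power. If the rounds are equal at 9.3 per area, this is about 4.8% to 2.8%; with the real 2014 counts it will differ.

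The 2014 counts should already be in the investigators' hands, so this is a recalculation and a rewording. It needs no extra participants and no change to the survey. The cost is a less favourable statement of power for the comparison with Option A.
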